### Target population

Children born by CS and exposed, in utero, to antibiotics immediately prior to birth will be compared with children born by CS and not exposed, in utero, to antibiotics immediately prior to birth. Children born vaginally during the same time period will be included as a control group.

### Eligibility criteria

All liveborn children for whom the birth year is between 2006 and 2018 will be included; the child and their mother’s healthcare record can be linked in primary care (THIN or CPRD) or secondary care (HES) databases; the mode of delivery, CS or vaginal delivery (VD), can be identified based on recording in primary care (THIN, CPRD) and/or secondary care (HES).

### Exclusion criteria

Children with missing delivery information will be excluded. In case of multiple births (eg, twins), one of the children will be randomly selected for inclusion to ensure independence of observations.

### Study outcomes

The primary outcomes for the study are the incidence of (1) asthma and (2) eczema. The main analysis for primary outcomes will be done separately in the primary care dataset and the secondary care (HES) dataset (the latter including only hospitals for which the year of antibiotic prescribing policy change is known).

Secondary outcomes are other allergic and allergy-related diseases, autoimmune diseases, infections and inflammation, other immune system-related conditions, neurodevelopmental conditions, less specific measures of child health, healthcare utilisation and maternal postpartum infectious morbidity (table 1).

**Table 1 T1:** The list of secondary outcomes

Outcome	Corresponding secondary objective	Datasets analysed	
		Primary care	Secondary care
*Health conditions and symptoms in children*	1.		
Other allergic and allergy-related conditions:	1.a		
Food allergy/intolerance		x	
Allergic rhinitis and conjunctivitis		x	
>1 allergy related disease (asthma, eczema, food allergy/intolerance, allergic rhinitis and conjunctivitis)		x	
Penicillin allergy*		x	
Anaphylaxis*		x	x
High risk of anaphylactic reaction (prescribing of automatic injection devices containing epinephrine)*		x	
Autoimmune diseases:	1.b		
Type 1 diabetes*		x	x
Coeliac disease*		x	x
Juvenile idiopathic arthritis*		x	x
Scleroderma/systemic sclerosis*†		x	x
Inflammatory myopathies*†		x	x
SLE*†		x	x
Autoimmune (idiopathic) ITP*		x	x
Juvenile pernicious (megaloblastic) anaemia*		x	x
Childhood vitiligo*†		x	
Infections and inflammation:	1 .c		
Neonatal sepsis (early and late onset)			x
Other sepsis*			x
Wheeze		x	
Upper respiratory tract infections*		x	
Lower respiratory tract infections*		x	x
Bronchiolitis*		x	x
Gastroenteritis*		x	x
Inflammatory bowel disease†		x	x
Urinary tract infections*		x	x
Antibiotic prescribing*		x	
Other immune system-related conditions:	1.d		
Necrotising enterocolitis			x
Leukaemia*†		x	x
Neurodevelopmental conditions:	1.e		
Cerebral palsy		x	
Autism spectrum disorder*		x	
ADHD*		x	
Less specific measures of child health:	1 .f		
Colic*		x	
Failure to thrive*		x	
*Healthcare utilisation in children*	2.		
Primary care consultations*		x	
Hospital admissions*			x
*Maternal outcomes (6 weeks post partum)*	3.		
Composite infectious morbidity (wound infection, endometritis/endomyometritis, pelvic abscess, maternal sepsis, death attributed to infection)		x	x
Endometritis/endomyometritis		x	x
Wound infection		x	x
Urinary tract infection/cystitis/pyelonephritis		x	x
Sepsis		x	x
Pelvic abscess		x	x
Maternal death (if infection related)*†			x
Antibiotic prescribing*		x	
Length of hospital stay*			x

*Exploratory outcome due to insufficient evidence base, including lack of longitudinal studies investigating the association between microbiota/early antibiotic exposure and outcome of interest;

†Tabulation if the outcome is very rare.

ADHD, attention deficit hyperactivity disorder; ITP, thrombocytopenic purpura; SLE, systemic lupus erythematosus.

### Data sources

To maximise the sample size, we will combine two UK-wide primary care research databases, THIN and CPRD, containing anonymised patient records of over 10% of the UK patient population.^19^ Both databases are broadly generalisable to the UK population in terms of demographics and medical condition prevalence.^20 21^ There is overlap between the databases at general practice level, with THIN and CPRD containing 37% and 46% unique practices, respectively. The databases do not use the same identifiers for patients or practices, but the overlapping practices can be identified reliably using patient registration, demographic and medical record information and the duplicates removed to create a combined THIN-CPRD dataset.^19 22^

Information on mothers and their children in the THIN-CPRD dataset can be linked using the family identification code, pregnancy codes, mother’s registered or estimated delivery date, child’s month of birth and gestational age at delivery. This is the optimal linkage method allowing identification of a large proportion of mother-child pairs.^23 24^ In addition, in both THIN and CPRD a large proportion of patients (about 30% and 60%, respectively) have linked hospital record data. Our estimates using THIN suggest that while the mode of delivery is accurately recorded in primary care (98% verified against hospital records), the recording is incomplete (the delivery mode is known for 55%–64% of children). The mode of delivery is well recorded in hospital records,^3^ therefore where linked hospital data are available, this will increase the sample of children with known mode of delivery where this is missing in primary care data.

To allow us to investigate more severe outcomes of interest requiring hospital admissions which are better recorded in secondary care, we will also create a mother-child linked database using anonymised Hospital Episode Statistics (HES) data collected for all NHS hospital admissions in England.^25^ This is a complex task requiring considerable expertise in record linkage, because in the UK there is no shared identifier to link maternal and child records in HES. It is, however, possible using deterministic and probabilistic linkage to attribute up to 98% of baby and mother secondary care records, as has been demonstrated in other large-scale studies of maternal and early life course research.^26 27^

We have a proposed linkage strategy which has already been validated by another recent study using matching algorithms based on HES data using organisation codes, admission dates, birth dates, general practice codes, sex, gestation and maternal age plus a number of other variables common to birth and maternity records. The database remains nationally representative for the main birth characteristics (such as gestational age, birth weight, sex and maternal age).^27^ The final output of this process will be a linked HES data set in which details of birth events and subsequent admissions of the children associated with these events can be elucidated.

HES alone, however, cannot be used to identify timing of prophylactic antibiotic administration and prophylactic antibiotics given. We will obtain the time point after which preincision antibiotic policy was introduced in each hospital from a national survey of maternity care providers in the UK. All maternity units undertaking CSs were included in the survey with a target response rate of 85%.

The exposure and outcome measures in the healthcare databases will be defined using the Read clinical code classification system used in primary care, and International Statistical Classification of Diseases and Related Health Problems 10th Revision (ICD-10) used for clinical diagnoses, the Office of Population Censuses and Surveys Classification of Surgical Operations and Procedures 4th revision (OPCS) for procedures and Healthcare Resource Groups (HRG) codes used in HES.

Recording of some variables in healthcare data, such as breastfeeding, is incomplete; we will therefore also investigate the trends in these variables by the mode of delivery using additional data sources such as the National Maternity Surveys.^28^

### Methods

We will compare rates of diagnosis of asthma and other outcomes of interest over time in children born by CS, comparing outcomes according to whether each mother received preincisional antibiotics.

In the primary analysis, we will estimate a probability that each mother received preincisional antibiotics according to year of birth, based on national policy uptake rates in the year of delivery for primary care data. For secondary care data, we will use the response from each hospital indicating the year of local policy implementation.

The major threat to validity in this observational comparison is not from case-mix confounders (indications for and incidence of CS have changed little over the study period); rather they relate to temporal changes in diagnosis and in the recording of outcomes and other exposures which impact on the number of cases identified in routine data. Patterns of diagnosis of childhood asthma, for example, have changed over time, in part driven by the revisions in the national asthma management guideline and the potentially conflicting compliance and prevalence issues faced in meeting specific indicators of the Quality and Outcomes Framework (QOF) introduced in 2004.^29 30^

An analysis reliant on adjustment for confounding factors is unlikely to succeed in controlling for these changes as it is unclear (1) what all the drivers of all these changes have been, (2) whether any covariates exist which accurately describe these changes without substantial missing data and (3) challenges in specification of a functional form for the relationship between these covariates and outcome.

In order to control for such temporal changes, we will use vaginally delivered (VD) children as a comparator, as this group will not have routinely received prophylactic antibiotics, but will have been subject to all the same temporal changes as those born by CS. Our study design will model the incidence of outcomes preintervention to predict the difference in disease incidence between babies born by CS (with antibiotics post cord-clamping) and VD (these are known to differ for some outcomes, such as asthma). From the period in which preincisional antibiotics are introduced, we will compare the observed incidence rate in CS children with a counterfactual incidence rate created by adding the VD-CS (postcord-clamping) difference to the observed incidence rate in VD children born postintervention. Subject to the assumption that the model of the difference between CS and VD rates is transferable across the time periods, differences between the observed and counterfactual CS event rates will be interpreted as likely to be caused by the change in practice.

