### Model validity

To assess model validity, we will explore changes in the case-mix of covariates over time in relation to delivery mode. Both maternal and child characteristics will be explored. The maternal characteristics considered will be: age at childbirth, ethnicity, parity, smoking status, body mass index before pregnancy, area deprivation coding, long-term allergy-related health conditions (asthma, eczema, allergic rhinitis and conjunctivitis), pregnancy and labour complications (premature rupture of membranes, postpartum haemorrhage, manual placental removal/retained products of conception) and antibiotic prescribing during pregnancy. The characteristics of the child considered include: gestational age, sex, ethnicity, birth weight, breastfeeding status and antibiotic prescribing during the first 5 years.

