Outcome events were randomly simulated according to the year-age event rates using a binomial random number generator, with increased rates in all those delivered by CS, and increased further in those who received antibiotics before skin incision. A risk ratio of 1.2 was used for increased risk of asthma with CS^32^ and then further increases with risk ratios from RR=1.10 to RR=1.20 (increasing in steps of 0.02) for the increase with antibiotics before skin incision rather than after cord-clamping.

Simulations were repeated 1000 times, and statistical power estimated by noting the proportion of simulations for which the lower limit of the 95% CI for the variable indicating whether antibiotics were given before skin incision was greater than a risk ratio of 1. We also recorded the estimates of the relative risk to assess attenuation bias created by misclassification.

The model which we fitted to analyse the simulation data included a trend term for the probability of receiving preincisional antibiotics with values 2006–2009=0, 2010=0.2, 2011=0.4, 2012=0.6, 2013=0.8, 2014–2018=1 with a zero value for those delivery vaginally (in the final analysis, we will use probabilities for each year obtained from the survey).

For the primary care data, we have 80% power of detecting a 16% relative increase in risk of asthma and over 90% power of detecting an 18% relative increase in risk, and being able to estimate them with a maximum of 15% underestimation from misclassification. For the HES admission data, we have over 80% power to detect a 10% relative increase in risk of asthma and 90% power to detect a 12% relative increase in risk with similar rates of underestimation due to misclassification.

The study will also be adequately powered to detect differences in the other primary outcome of interest (eczema) as incidence of clinician-diagnosed eczema is higher than asthma incidence in children in the UK.^33–35^

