### Analysis

The primary and secondary outcomes will be analysed using a Poisson regression model to estimate the relative risk of developing each outcome with preincision compared with postcord clamping antibiotics. We will assess for overdispersion and if high, consider other models, such as a negative binomial. Appropriate considerations will be made to allow for the autocorrelation of data. We will look at the autocorrelation and partial autocorrelation plots to ensure any autocorrelation is accounted for. An adjustment for calendar time will be included in the model to allow for season effects. We will include terms for year, age and the interaction between them and mode of delivery (CS or vaginal). The key outcome parameter will be estimated by an additional term to identify those who receive preincision rather than postcord clamping antibiotics.

Rather than being described in dichotomous form, we will estimate the probability of preincision antibiotics using data from the national survey and known hospital policy. The estimated coefficient will provide an estimate of the change in policy, adjusting for misclassification.

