#### Sensitivity analyses

Sensitivity to population changes:

Analysis assessing the impact of the timing of the prophylactic antibiotic policy change, including comparison of analysis restricted to the years 2006–2010 (before the change in the NICE guideline) compared with years where over 50% of hospitals had introduced the policy.Analysis of the primary outcomes in the full HES dataset (including data for the hospitals that do not respond to the survey and therefore preclude us linking information about prophylactic antibiotic policy at hospital level) using the estimated probability of introduction of preincisional antibiotics according to calendar year, to investigate the consistency of findings.Analysis investigating the impact of the data recording quality (restricted to HES-linked records in THIN-CPRD database as the most accurate source of records for the mode of delivery).Exploratory sensitivity analysis employing the discordant sibling approach (restricting the analysis to women who gave birth by CS more than once during the study period including before and after the change in the prophylactic antibiotic policy compared with women who gave birth by VD more than once during the study period) to control further for family-related genetic and environmental factors.

Sensitivity to model changes:

Analysis exploring whether the results are robust to the inclusion of a random effect for hospital.

Subgroup analyses:

Exploratory subgroup analysis in HES mother-child linked database by prophylactic antibiotic type administered according to the individual hospital policies to investigate the potential impact of different antibiotics (cefuroxime alone, co-amoxiclav alone, cefuroxime+metronidazole) on child outcomes.Exploratory subgroup analysis by the type of CS (it is hypothesised that children delivered by elective CS have a higher likelihood of asthma and related outcomes and are more likely to be exposed to in-utero antibiotics for longer than children born to women having an emergency CS).

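### Elective and emergency CS share one delivery-mode term although the protocol expects their asthma risk to differ, so a change in their mix that tracks exposure would enter the antibiotic estimate

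*Protocol article*

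**What the plan says.** All of this is in the protocol article.

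- **Methods** takes the CS-VD difference from the period of post-clamping antibiotics and adds it to the later VD rate to form the counterfactual CS rate. Departures from it are read as likely effects of the change in practice, "Subject to the assumption that the model of the difference between CS and VD rates is transferable across the time periods".
- **Methods** also plays down case-mix, on the ground that "indications for and incidence of CS have changed little over the study period".
- **Analysis** fixes the model: "We will include terms for year, age and the interaction between them and mode of delivery (CS or vaginal". The bracket names two levels only. One further term carries the preincision effect.
- **Sensitivity analyses**, under subgroup analyses, plans an "Exploratory subgroup analysis by the type of CS", and gives as a reason that "it is hypothesised that children delivered by elective CS have a higher likelihood of asthma and related outcomes".
- **Model validity** says "we will explore changes in the case-mix of covariates over time in relation to delivery mode" and lists maternal and child characteristics. CS type is not among them.
- **Estimates of sample size and statistical power** uses a single value for all CS in the simulation: "A risk ratio of 1.2 was used for increased risk of asthma with CS".

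**The concern.** If elective and emergency CS carry different asthma risks, as the protocol hypothesises, the single CS-VD difference is a weighted mean of two type-specific differences, with the elective share as the weight. It carries over from the unexposed to the exposed births only if that share stays the same, apart from any trend the model removes.

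Stable indications and a stable overall CS rate do not by themselves fix the split between planned and emergency operations. A change in the split that runs with exposure alters the CS baseline without any antibiotic effect, and the key coefficient picks it up. A rise in elective share would imitate harm; a fall would hide it. No planned descriptive table shows the split directly, and no planned model for the key coefficient holds it constant.

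**Working it through.** **The plan's own figures.** Table 2 is consistent for primary care: 7173 + 20 378 = 27 551 events, and 27 551 / 3 007 670 person-years = 9.2 per 1000. The simulated power cannot be rebuilt because the year-age event rates are not published. That is no sign of error, and the point does not rest on it.

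**Inputs not in the documents.** The elective share and the elective v emergency RR are not given. I assume a share s0 = 0.35, a 10-point rise or difference (s1 = 0.45), and RR k = 1.3.

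**Step 1: full pass-through.**

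Spurious RR = (1 + s1(k − 1)) / (1 + s0(k − 1)) = (1 + 0.45 × 0.3) / (1 + 0.35 × 0.3) = 1.135 / 1.105 = 1.027.

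On the log scale this is 0.0267. That is 18% of log(1.16) = 0.148, the primary care target, and 28% of log(1.10) = 0.0953, the HES target.

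Wider assumptions (start 30-40%, rise 5-10 points, k 1.1-1.3) give a range:
- smallest: 1.045 / 1.040 = 1.005
- largest: 1.12 / 1.09 = 1.028

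**Step 2: how much passes through the planned model.** I fitted Poisson models to expected counts with no antibiotic effect. Cells were birth year by age by mode, scaled to the Table 2 person-years and events, with year (birth year) as categories, age, and age-by-mode. In primary care, exposure took the stated values "2006–2009=0, 2010=0.2, 2011=0.4, 2012=0.6, 2013=0.8, 2014–2018=1". In HES I assumed five equal groups of hospitals adopting in 2010 to 2014, with exposure switching from 0 to 1 at adoption. Two-level mode coding gave these spurious RRs:

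| Setting | Change in elective share | Linear year-by-mode | Categorical year-by-mode |
|---|---|---|---|
| Primary care | along the 2010-2014 uptake | 1.027 | exposure not estimable |
| Primary care | straight line 2006-2018 | 1.000 | exposure not estimable |
| HES | national, along the uptake | 1.003-1.004 | 1.000 |
| HES | national, straight line | 1.000 | 1.000 |
| HES | rises at each hospital's own adoption | 1.027 | 1.027 |
| HES | constant over time, higher in early adopters | about 1.02 | about 1.02 |

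For the last row, a share falling evenly from 45% in the earliest to 35% in the latest adopters gives 1.015 (linear) and 1.017 (categorical). Setting the two earliest groups at 45%, the middle at 40% and the two latest at 35% gives 1.018 and 1.020.

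In primary care the exposure value depends only on birth year among CS births, so a full set of year-by-mode terms leaves it inestimable. Some smoother form is needed, and a shift shaped like the uptake then passes through.

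**Step 3: chance of a false harm signal in primary care.** With a start of 40%, a 10-point rise along the uptake and k = 1.2, the spurious RR is 1.10 / 1.08 = 1.019. The chance that the lower 95% limit exceeds 1 is 3.7% with a linear year-by-mode term and 7.9% without one, against a nominal 2.5%.

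**Step 4: three-level coding.** With elective CS, emergency CS and vaginal as separate modes, each with its own year and age terms, and one common preincision coefficient, the spurious RR was 1.000 in every estimable scenario. The standard error hardly moved (for example 0.0255 to 0.0256 in HES with linear year-by-mode terms).

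**The case against.** The strongest reply is that no change in mix is shown. The protocol says indications and incidence were stable, states transferability openly as an assumption, and includes year-by-mode interactions. This stands in large part: the bias is conditional, and a straight-line drift is removed by a linear term.

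A reader might infer more, namely that a national rise in elective share would enter the HES result in full. With the standard error implied by 80% power at RR 1.10, 0.0953 / (1.960 + 0.842) = 0.034, a spurious RR near 1.028 would lift the false-harm rate to about 12%, and a fall of that size would cut power to about 52%. The documents do not support that reading. In the main HES analysis exposure is set by each hospital's year of implementation, so exposed and unexposed CS births occur in the same year and the year-by-mode terms take up most or all of a national shift.

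Three further replies stand in part.
- The subgroup analysis by CS type holds type constant and could reveal a mix effect. It is exploratory, however, and leaves the key coefficient as it is.
- Gestational age, parity and membrane rupture, which are on the case-mix list, may partly reflect planned or emergency delivery. They are indirect markers.
- The random effect for hospital bears on differences between hospitals. An intercept shared by CS and VD births does not by itself correct a CS-VD difference that varies between hospitals, nor a change within a hospital at adoption.

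It is also fair that CS type may be incompletely recorded in primary care, where mode itself is known for only 55-64% of children before linkage. A level for unrecorded type would be a mixture whose composition could drift. That argues against recoding the main primary care model.

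**Conclusion.** The point holds in a conditional form. On the protocol's own hypothesis, pooling the two CS types leaves the key coefficient open to a change in elective share that tracks exposure, and no planned check or adjustment addresses CS type directly.

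The exposed routes are narrow. In primary care it is a shift that follows the uptake curve. In HES it is an elective share that differs between early- and late-adopting hospitals or moves with local adoption. Under the assumed 10 points and RR 1.3 the size is a few per cent, which matters more against the 10-12% effects targeted in HES than against the 16% in primary care. It scales with both assumptions and vanishes if the elective share does not track exposure or the two types carry equal risk. It is a reason to improve the model, and no evidence that the results will be biased.

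**What to change.** 1. **HES main model (Analysis).** Replace the two-level mode term by elective CS, emergency CS and vaginal, with the same year and age interactions. Keep one common preincision coefficient as the key result.
2. **Model validity.** Add CS type to the characteristics, tabulated by year and, in HES, also by hospital adoption status.
3. **Primary care (Sensitivity analyses).** Keep the two-level main model and add the three-level model as a sensitivity analysis in records with known CS type, for example the HES-linked ones.

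Cost: a few more parameters in the HES model, using a variable already needed for the planned subgroup analysis, and a smaller sample for the primary care sensitivity analysis.
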